## Abstract

**Background:**

Transgender women in the U.S. have an alarmingly high incidence rate of HIV infection; condomless anal and vaginal sex is the primary risk behavior driving transmission. Young transgender women are the subpopulation at the highest risk for HIV. Despite this, there are no published randomized controlled efficacy trials testing interventions to reduce sexual risk for HIV among this group. This paper describes the design of a group-based intervention trial to reduce sexual risk for HIV acquisition and transmission in young transgender women.

**Methods:**

This study, funded by the National Institutes of Health, is a randomized controlled trial of a culturally-specific, empowerment-based, and group-delivered six-session HIV prevention intervention, Project LifeSkills, among sexually active young transgender women, ages 16-29 years in Boston and Chicago. Participants are randomized (2:2:1) to either the LifeSkills intervention, standard of care only, or a diet and nutrition time- and attention-matched control. At enrollment, all participants receive standardized HIV pre- and post-test counseling and screening for HIV and urogenital gonorrhea and chlamydia infections. The primary outcome is difference in the rate of change in the number of self-reported condomless anal or vaginal sex acts during the prior 4-months, assessed at baseline, 4-, 8-, and 12-month follow-up visits.

**Discussion:**

Behavioral interventions to reduce sexual risk for HIV acquisition and transmission are sorely needed for young transgender women. This study will provide evidence to determine feasibility and efficacy in one of the first rigorously designed trials for this population.

**Trial registration:**

ClinicalTrials.gov number, NCT01575938, registered March 29, 2012.

## Background

Available evidence suggests that the prevalence of HIV infection is disproportionately high among transgender women, including young transgender women (YTW) both in the U.S. and globally. A meta-analysis of the global burden of HIV infection in transgender women found an HIV prevalence of 19.1% (95% CI = 17.4-20.7) and a 49-fold increased odds of HIV infection compared with all adults of reproductive age [1]. In the U.S., a meta-analysis of 29 studies [2] found a prevalence of 27.7% laboratory-confirmed HIV infection (four studies) and 11.8% self-reported (18 studies) among transgender women. Furthermore, data from local testing of over 500 transgender women (with no known prior positive HIV test results) in Miami, San Francisco, and Los Angeles found the highest number of new infections among those ages 20-29 years (i.e., 45% of all cases) [3], suggesting disproportionate HIV incidence among younger transgender women in particular.

Condomless sex, particularly anal and vaginal sex, represents transgender women’s primary risk for HIV acquisition and transmission with high rates of sexual risk reported in small studies, including among YTW [2, 4, 5]. Recent findings suggest that inconsistent condom use during anal sex with HIV-infected partners offers little to no protection against HIV infection, and that consistent condom use over time is rare [6]. While biomedical interventions, including pre-exposure prophylaxis (PrEP), have demonstrated safety and efficacy to prevent HIV infection among men who have sex with men and transgender women in clinical trials [7–9], analysis of uptake of PrEP in practice has been limited among transgender women (<10%) [10]. Furthermore, among transgender women taking PrEP in the iPrex trial, evidence suggests medication adherence was suboptimal [11]. Given challenges with both uptake and adherence to PrEP, combination HIV prevention approaches, including promotion of condom use, are more effective than PrEP alone [12] in high risk populations and are recommended by the Centers for Disease Control and Prevention (CDC) [13].

Only a small number of (non-randomized) interventions have attempted to reduce sexual risk in transgender women. In a critical review of behavioral interventions for HIV prevention among transgender women undertaken by members of our research team [14], we identified only five interventions formally tested for transgender women (one for YTW, in particular). Four of 5 studies documented small to moderate effects with evidence of diminishing effects over time [14]. None of these studies have been of sufficient quality to be included in the CDC’s compendium of HIV prevention interventions (https://www.cdc.gov/hiv/research/interventionresearch/compendium/).

### Study objectives

The primary objective of this study is to test the efficacy of the LifeSkills intervention to reduce sexual risk for HIV acquisition and transmission among young transgender women, ages 16-29 years. A secondary objective is to test hypothesized social, cognitive and behavioral mediators of the intervention effect.

## Methods/design

### Design

This study is a three-arm randomized controlled trial targeting young transgender women, ages 16-29 years who are at high risk of HIV acquisition or transmission due to sexual risk behavior, conducted in two cities in the U.S.: Boston and Chicago. Participants are randomized to receive the LifeSkills group-based intervention, standard-of-care preventive care only, or a time- and attention-matched group-based control intervention (non-active). All study groups receive repeat standard preventive care which consists of HIV testing with pre-posttest counseling and urogenital screening for gonorrhea and Chlamydia. Participants who are randomized are followed for 12 months with visits conducted at 4-month intervals: 4, 8, and 12-month post-randomization (Fig. 1).

**Fig. 1 Fig1:**
[figure not shown]
Flow chart of study intervention process

### Identification and recruitment of participants

Participants are recruited via outreach to community-based organizations and events, public spaces (e.g., bars and clubs), and social media outreach and advertisement (e.g., Facebook, Craig’s List); and through direct outreach by peer recruiters and transgender community leaders. Grounded in community-based participatory research principles [15], recruitment is carried out with input from local transgender communities in each city. Eligibility criteria include: (1) ages 16-29 years; (2) assigned male sex at birth and, at the time of enrollment, self-identify as a woman, female, transgender woman, transfemale, male-to-female (MTF), or on the trans feminine spectrum; (3) English-speaking; (4) no plans to move from the local area during the 12-month study period; and (5) self-reported sexual risk in the previous 4 months (i.e., condomless anal or vaginal intercourse; anal or vaginal intercourse with more than one sexual partner; anal or vaginal sex in exchange of money, food, shelter; or diagnosis with HIV or another sexually transmitted infection). Participants are excluded if they are unable to provide assent/consent due to severe mental/physical illness or intoxication; or if they are actively suicidal at the time of enrollment. Potential participants may enroll when these conditions resolve.

### Randomization

On a rolling basis, cohorts are assembled for a randomization visit (*n* = 10-15) in which individuals are randomized in blocks of 5 (2:2:1) to either LifeSkills (LS), standard of care (SOC) or diet and nutrition (DN) attention control. The random assignments are generated by computerized random number generator. Random assignments are concealed from both participants and study staff until they are revealed at the randomization visit, after each complete cohort has been assembled.

### Description of the intervention: Project LifeSkills

The LifeSkills intervention was developed to address the specific structural, developmental, and interpersonal challenges to sexual safety based upon the well-documented social realities of YTW [16, 17] and demonstrated feasibility and initial efficacy in a CDC-funded pilot trial [16]. Theorized mediators of the intervention effect include empowerment processes (e.g., increases in collective self-esteem and integration) as well as traditional HIV related prevention and health promotion targets (i.e., HIV-related knowledge, motivation, and behavioral skills). Empowerment has been described as a social process in which individuals (and communities) gain mastery over their lives [18]; it typically involves the development of skills, knowledge, and confidence which allows them to overcome obstacles in their personal and communal lives [18–21]. Empowerment processes may facilitate behavior change, building on the resiliencies, strengths, and capabilities of YTW as a collective community [22, 23], and help to buffer the effects of social and economic marginalization. There is mounting evidence that social and economic factors are associated with high rates of HIV transmission and adverse HIV-related outcomes in high risk groups [24]. The Information, Motivation, Behavioral Skills (IMB) model integrates theory and research from both health and social psychology literatures and has been applied to a wide array of wellness-promotion and health behaviors [25, 26]. With respect to HIV prevention, IMB focuses on the set of informational, motivational, and behavioral skills that are conceptually and empirically associated with safer sex. The Life Skills intervention targets information, motivation, and behavioral components consistent with the IMB model for HIV sexual risk reduction in YTW.

The LifeSkills curriculum is manualized and includes six sessions (Table 1): 1: Pride, 2: communication and respect; 3: skills building, 4: knowledge and self-protection, 5: partner negotiation, 6: tying it all together) to communicate basic HIV-related information (e.g., transmission modes and related risks), develop motivation (e.g., to protect oneself), and promote behavioral skill development (e.g., condom use, sexual partner communication and negotiation) through an empowerment-based approach [17]. The Life Skills curriculum incorporates interactive activities, in-depth discussions, videos, games, and role-plays to help participants develop, practice, and integrate new skills into “real-life” situations. Integrated throughout the curriculum is information on gender transition/affirmation and experiences and scenarios specific to transgender women’s experiences. Each session begins by asking participants to share one proud moment that occurred in the previous week to focus on the positive aspects of their lives and set the tone for the intervention session. Each session ends with a ceremony in which participants are given a small gift (i.e., key chain, mirror) and asked to describe one thing they learned from the day’s session that they could teach other young women, which serves to reinforce key intervention messages. During the sixth session, participants develop a personal risk reduction plan designed to identify risk behavior and alternative behavior options. The intervention is delivered by two trained transgender women in 2-h small-group sessions twice a week for three consecutive weeks. Facilitators are trained using a standard protocol. To monitor intervention fidelity, intervention sessions are audio-recorded, reviewed, and rated by an outside evaluator. Study facilitators also complete self-rating forms. Feedback is provided in weekly supervision sessions by the study coordinator at each site based on review of rating forms.

**Table 1 Tab1:** Summary of LifeSkills theoretical constructs and session topics

Session	Title	Theoretical Constructs:
1	Pride	Transgender adaptation/ integration; collective self-esteem/empowerment
2	Communication and Respect	Information (HIV knowledge), skills building for communication
3	Skills Building – Housing, Employment, Medical Services	Building skills to meet basic needs and applying communication skills
4	Knowledge and Self-Protection	Information, Motivation (attitudes, norms, and intentions for safer sex), basic skill building for condom use.
5	Partner Negotiation	Behavioral skills (discussing sex and condom use with sexual partners), sexual contexts, drug/alcohol use
6	Tying it all Together	All Constructs Reviewed

### Time- and attention-matched control: Diet and nutrition

The time and attention-matched control intervention is also manualized and delivered at the same time/place as the LifeSkills intervention in six sessions and facilitated by a transgender woman. Control manual content was drawn from recommendations of the United States Department of Agriculture (USDA; https://www.choosemyplate.gov). The control intervention sessions include: an introductory session, followed by five sessions devoted to the major food groups. Control group sessions include interactive activities and games and are of similar length as the LS sessions.

### Standard-of-care prevention services

Participants in all study conditions receive pre-posttest counseling coupled with HIV screening (i.e., third generation testing algorithms at each site for those reporting HIV-negative or unknown status) per the RESPECT-2 protocol [27] and urogenital gonorrhea and chlamydia sexually transmitted infections (STIs; first catch urine via nucleic acid amplification testing, NAAT).

### Study assessments

Participants complete a baseline study visit comprised of standardized assessment via computer-assisted personal-interviewing (CAPI; including both interviewer- and self-administered questions) as well as screening for HIV/STIs. Follow-up CAPI assessments are conducted at 4, 8 and 12-month follow-ups, with repeat HIV/STI screening at the 4 and 12-month visits.

Primary Outcome: Condomless Anal or Vaginal Sex. Items assessing sexual behavior were self-administered and adapted for YTW from the AIDS Risk Behavior Assessment (ARBA) [28]. All items assessed sexual behavior in the prior 4 months. The basis for construction of the primary outcome is a set of sequential questions asking the participant to estimate the number of anal and vaginal sex partners they had in the recall period and the number of condomless sex acts by type of sex (vaginal, anal) and position (receptive, insertive) with these partners. A lead-in question asks about history of gender affirming vaginosplasty which determines deployment of questions regarding vaginal sex by position (receptive or insertive).

Mediators: Collective self-esteem, transgender adaptation and integration, HIV knowledge, motivation, behavioral skills. The collective self-esteem scale (CSES) [29] is a 16-item self-report measure that assesses a person’s thoughts and feelings regarding their social group (modified to include reference to the “transgender community”). Using a seven-point scale, participants indicated the degree to which they agree or disagree with statements regarding the reference group (1-strongly disagree to 7-strongly agree). The items form four subscales (four items each): membership (e.g., “I am a worthy member of the transgender community”); private (e.g.,“I feel good about the transgender community”); public (e.g., “In general, others respect the transgender community”); identity (e.g., “Being part of the transgender community is an important reflection of who I am”). The TG-AIM is a 15-item measure that assesses adjustment and experiences that are specific to gender identity [30]. This validated measure uses a 4-point Likert scale (0 = never, 1 = rarely, 2 = occasionally, 3 = frequently) to assess four subscales: (1) coping and gender reorientation efforts; (2) gender locus of control; (3) gender-related fears subscale; (4) psychosocial impact of gender status subscale. Although this scale has been used in previous research with transgender adults [30, 31], we have adapted this measure as appropriate for YTW.

To measure HIV knowledge, we adapted the brief HIV Knowledge Questionnaire (HIV-KQ-18) [32] for use with YTW (total 20 items). Motivation and behavioral skills are measured using items adapted from previous HIV prevention studies [33–35]. Motivation to practice safer behavior is assessed as three separate dimensions: attitudes, norms, and behavioral intentions to engage in HIV-preventive actions (total scale = 24 items). Behavioral skills for HIV prevention is assessed with 12 items that asked how “hard” or “easy” it was for participants to implement a variety of skills, including discussing sex and condom use with sexual partners, and acquiring and using condoms. Response options range from 1 = “Very Hard to Do” to 5 = “Very Easy to Do.”

### Statistical analysis

Initially, the distribution of all variables will be assessed, as will the correlations between all study variables and the primary and secondary outcomes. We will also assess for patterns of missing data. The primary anticipated reason for missing data is attrition due to loss to follow-up. We estimate 20% attrition to the 12-month follow-up assessment (375 randomized leading to 300 completers of the intervention). Outcome variables will be examined to determine which distributional models (e.g., Gaussian, Poisson) are most appropriate for subsequent statistical procedures. The primary analysis will compare differences in risk behavior at the month 4 visit between study arms using an intent-to-treat approach. Between-group differences at the month 8 and month 12 visits will similarly be compared. We will use mixed effects models with properly-chosen (based on the distribution of dependent variable) link functions to analyze longitudinal data for each study aim and examine the difference in the rate of change between intervention groups for the outcome variables. Mixed effects models explicitly model individual change across time and allow for unequal number of observations per individual (e.g., missing time points) [36]. If the 6-session Life Skills intervention does work to reduce sexual risk-taking behaviors among the sample in significantly greater magnitude than the comparison conditions, we will assess the extent to which this relationship works through several possible mediators, including increases in collective self-esteem/empowerment, transgender adaptation and integration, and HIV related information, motivation, and behavioral risk-reduction skills. For hypothesized mediators that are significantly changed by the intervention (i.e., the rate of change differed by treatment assignment), we will conduct mediation analysis to determine whether the effect of the intervention on the primary, acute outcome (i.e., at month 4 follow-up) was through the hypothesized mediator(s) [37].

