### Sample size calculation

The primary power analysis is based on detecting a 40% (or greater) difference in the number of condomless sex acts between groups over the course of the study (per estimate of effect size in the pilot study) [16], expecting all groups to show improvements from baseline. Based on these data, with a power of 85% and alpha level of 0.05 and factoring in 20% attrition, we estimate needing 300 completers of the proposed intervention (LS = 120; SOC arm = 120; DN time and attention-matched control = 60).

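### Group delivery of LifeSkills and DN is not reflected in the described model or the 85% power; with a positive within-group ICC the LS-SOC standard error is modestly understated

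*Protocol article*

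**What the plan says.** **Randomization.** Cohorts of 10-15 people are assembled for a joint visit, at which "individuals are randomized in blocks of 5 (2:2:1) to either LifeSkills (LS), standard of care (SOC) or diet and nutrition (DN) attention control".

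**Delivery.** The section on Project LifeSkills states: "The intervention is delivered by two trained transgender women in 2-h small-group sessions twice a week for three consecutive weeks". The Design section calls the DN control group-based, and its own section gives it six sessions at the time and place of the LS sessions. No group sessions are described for SOC.

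**Analysis.** The Statistical analysis section plans mixed effects models with a link function suited to the outcome. It explains the choice in this way: "Mixed effects models explicitly model individual change across time and allow for unequal number of observations per individual". No effect for treatment group, cohort or facilitator is named.

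**Sample size.** The calculation rests on "detecting a 40% (or greater) difference in the number of condomless sex acts between groups over the course of the study", "with a power of 85% and alpha level of 0.05 and factoring in 20% attrition". It arrives at 120 LS, 120 SOC and 60 DN completers. The Statistical analysis section adds that 375 are randomized. Neither section gives an ICC or a design effect.

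**The concern.** Participants are randomized one by one, but two of the three arms are treated in groups. Members of one LS group share sessions and facilitators. The article also expects LS to work partly through collective processes (collective self-esteem, integration, empowerment), by way of discussion and role-play. Some correlation of post-baseline outcomes within an LS group is therefore plausible, with no counterpart in SOC. This is a partially nested design.

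A model that allows only for repeated visits within a person leaves this component out of the variance of the LS mean. If the correlation is positive, and taken by itself, confidence intervals are too narrow, type I error exceeds 5% and true power is below 85%. The error would favour an efficacy claim in a trial that the Discussion presents as a possible basis for endorsed dissemination. A later analysis plan could add the missing term, but could not restore the power of a sample size fixed without it.

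**Working it through.** **Inputs from the article:** 85% power and alpha 0.05; 120 LS and 120 SOC completers; 20% attrition; 2:2:1 allocation; cohorts of 10-15.

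**Assumptions:** a two-sided test; the 85% refers to LS v SOC (no pairwise contrast is named) and is correct under independence; each cohort forms one LS and one DN group; the ICC ranges over 0.01-0.10; the usual design-effect formula is an adequate approximation for the count outcome.

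**Step 1: the plan's own figure.** 300/(1 - 0.20) = 375, which agrees with the stated number randomized. Attrition is thus the only visible inflation. The 300 cannot be reproduced, because no mean, SD or overdispersion is given.

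**Step 2: group sizes.** LS: 2/5 x 10 = 4 to 2/5 x 15 = 6. DN: 1/5 x 10 = 2 to 1/5 x 15 = 3. The stated power refers to completers, so the matching LS group size is m = 0.8 x 4 = 3.2 to 0.8 x 6 = 4.8. Number of cohorts: 375/15 = 25 to 375/10 = 37.5.

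**Step 3: LS v SOC with a group effect in LS only.**
- Design effect in LS: DE = 1 + (m - 1) x ICC; in SOC it is 1.
- Variance ratio of the contrast with equal arms: r = (DE + 1)/2.
- Noncentrality under independence: 1.960 + 1.036 = 2.996.
- Power = Phi(2.996/sqrt(r) - 1.960).
- Type I error of the uncorrected test = 2 x [1 - Phi(1.960/sqrt(r))].

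Example, ICC 0.05 and m = 4.8: DE = 1 + 3.8 x 0.05 = 1.190; r = 1.095; sqrt(r) = 1.046; power = Phi(2.863 - 1.960) = 81.7%; type I error 6.1%.

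| ICC (assumed) | m | DE in LS | SE ratio sqrt(r) | Power | Type I error |
|---|---|---|---|---|---|
| 0.01 | 3.2 | 1.022 | 1.005 | 84.6% | 5.1% |
| 0.01 | 4.8 | 1.038 | 1.009 | 84.3% | 5.2% |
| 0.05 | 3.2 | 1.110 | 1.027 | 83.1% | 5.6% |
| 0.05 | 4.8 | 1.190 | 1.046 | 81.7% | 6.1% |
| 0.10 | 3.2 | 1.220 | 1.054 | 81.2% | 6.3% |
| 0.10 | 4.8 | 1.380 | 1.091 | 78.4% | 7.2% |

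**Step 4: the offset from shared cohort effects.** Arms are randomized within cohort, so an effect common to the whole cohort drops out of LS minus SOC, yet a model without cohort counts it as noise. Let the residual variance be 1, the cohort variance c and the LS group variance g. Per cohort, the true contrast variance is 2/m + g, and the variance that the unadjusted model reports is (2 + 2c + g)/m. They are equal when c = (m - 1)g/2. With m = 5:
- c = 0, g = 0.05: 0.450 against 0.410, true/reported SE = 1.048.
- c = 0.10, g = 0.05: 0.450 against 0.450, ratio 1.000.
- c = 0.05, g = 0.02: 0.420 against 0.424, ratio 0.995.

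At m = 5, a full offset therefore needs a cohort variance of twice the group variance. At m = 3.2-4.8 it needs 1.1 to 1.9 times.

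**The case against.** The strongest reply is that this argues from silence. The sentence on mixed models states a general property of the method and does not list this trial's random effects. Nothing in the article rules out a group term, and an article may leave the random-effects structure to a fuller document. A reader might infer that the plan treats participants as independent, or that the groups are closed; the article says neither. What remains is that the article does describe a model, explains it only by within-person change, and gives a power figure whose sole visible inflation is for attrition. Because the 300 cannot be reproduced, an allowance hidden inside it cannot be excluded either.

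The second reply is that direction and size are not known, and this stands. No ICC is given, and at 0.01 the loss is under one percentage point. City and calendar time should not be counted as sources of LS clustering: SOC members of the same cohort share them, they cancel in the contrast, and leaving them out makes the standard error too large. Only sessions and facilitators are specific to the arm. The article gives no ratio of cohort to group variance, so the offset cannot be relied on. It is a reason to model both levels, not to omit both.

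A reader might also reach larger figures, such as 76.4% power and 8.0% type I error at ICC 0.10, by using groups of 6. That sets enrolled group sizes against completer counts, and the article does not support the combination.

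**Conclusion.** The point holds in conditional form. The design is partially nested, and neither the described model nor the power statement reflects it. If the post-randomization ICC within LS groups is positive and no cohort effect offsets it, the LS-SOC standard error is understated by a factor of about 1.03-1.05 at ICC 0.05 and 1.05-1.09 at ICC 0.10. The 85% power then becomes 82-83% or 78-81%, and the 5% type I error becomes 5.6-6.1% or 6.3-7.2%. At ICC 0.01 the effect is negligible.

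The flat statement that standard errors are too small and power too high goes further than the article allows: it needs an ICC that is not given and ignores the cohort offset. The ICC range, the two-sided test and the assignment of the 85% to LS v SOC are assumptions. This should be fixed, but it is not a defect that by itself invalidates the trial.

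**What to change.** 1. Specify a partially nested mixed model with cohort as a blocking factor and a treatment-group random effect in LS and DN only.
2. Let the group effect act on post-baseline outcomes, or on change, and not on baseline, which precedes the sessions. A plain group intercept across all visits would impose clustering at baseline and miss group variation in change.
3. State beforehand whether LS and DN share one group variance. DN groups of 2-3 say little about a variance of their own.
4. Use small-sample degrees of freedom based on the number of groups, with about 25-38 cohorts.
5. Restate the power over a declared ICC range, for example 0.01 to 0.10, name the contrast to which the 85% applies, and say that no more participants will be enrolled on this account.

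Cohort and group membership are known from randomization, so no new data are needed. The cost is slightly wider intervals where the group variance is positive, a slightly lower stated power, and a somewhat more complex model.

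### Mediators are screened on a rate of change, but the outcome they must explain is at month 4, so a mediator effect that fades may never be tested

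*Protocol article*

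**What the plan says.** All of the following is from the protocol article.

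- **Objective** (Study objectives): "A secondary objective is to test hypothesized social, cognitive and behavioral mediators of the intervention effect".
- **First condition** (Statistical analysis): mediation is examined if LifeSkills (LS) lowers risk behaviour "in significantly greater magnitude than the comparison conditions".
- **Second condition** (same section): "For hypothesized mediators that are significantly changed by the intervention (i.e., the rate of change differed by treatment assignment), we will conduct mediation analysis".
- **Outcome to be explained** (same sentence): the question is whether the intervention effect "on the primary, acute outcome (i.e., at month 4 follow-up") ran through the mediator.
- **Where else rate of change appears:** the Abstract attaches it to the primary outcome, assessed at baseline and months 4, 8 and 12. Statistical analysis attaches it to the mixed models of longitudinal data for each study aim, after separately listing arm comparisons at months 4, 8 and 12.
- **Timing of any mediator change:** the sessions run over three weeks (Description of the intervention). Background says that four of five earlier studies showed "small to moderate effects with evidence of diminishing effects over time".

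**The concern.** One sentence selects mediators on one quantity (a difference between arms in rate of change) and then uses them to explain an outcome defined on another (the level of risk behaviour at month 4). The two agree if a mediator's early change persists. They part company if it fades. An early rise followed by decline leaves little or no linear trend across 12 months, and can even reverse its sign.

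The design makes that pattern plausible, since the intervention is over within three weeks and earlier interventions in this field lost effect with time. At stake is the secondary objective: a mediator that did carry the month-4 effect could be left out of the mediation analysis because of what happened to it after month 4.

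**Working it through.** **1. The plan's own figures.** The article gives no figure for the mediation analysis. Its sample size is consistent: 300/(1 − 0.20) = 375 randomized, and 300 split 2:2:1 is 120/120/60. The calculation below uses LS v standard of care, 120 v 120.

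**2. Inputs.**
- From the article: visits at 0, 4, 8 and 12 months; 120 completers in each of the two arms; alpha 0.05. The article does not say whether alpha is one- or two-sided; two-sided is assumed.
- Assumed, not in the article: mediator shift d = 0.4 SD at month 4; within-person correlation r = 0.3, 0.5, 0.7 (compound symmetry); unit variance; normal approximation; a linear time term for the slope screen.

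**3. Slope implied by each trajectory.** The linear-slope weights at 0, 4, 8 and 12 months are (−6, −2, 2, 6)/80. Applied to the arm difference at each visit:

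| Trajectory of the arm difference | Slope per month | Over 12 months, as a multiple of d |
|---|---|---|
| Sustained (0, d, d, d) | (−2 + 2 + 6)d/80 = 0.075d | 0.90 |
| Half faded (0, d, 0.75d, 0.5d) | (−2 + 1.5 + 3)d/80 = 0.03125d | 0.375 |
| All faded (0, d, 0.5d, 0) | (−2 + 1 + 0)d/80 = −0.0125d | −0.15 |

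Under compound symmetry these multiples do not depend on d or r. They depend only on the trajectory.

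**4. Power of the slope screen.** SE = √[((1 − r)/80) × (2/120)]. At r = 0.5 this is 0.01021. Power in the right direction is Φ(slope/SE − 1.96).
- Sustained: 0.030/0.01021 = 2.94; power 84%.
- Half faded: 0.0125/0.01021 = 1.22; power 23%.
- All faded: −0.005/0.01021 = −0.49; 0.7% in the right direction, and about 7% significant in the wrong direction.

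**5. Power of a month-4 contrast.** With baseline adjustment, SE = √[(1 − r²) × (2/120)]. At r = 0.5 this is 0.1118, so 0.4/0.1118 = 3.58 and power is 95%, whatever happens after month 4.

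**6. Range over the assumed correlation (d = 0.4).**

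| Test | r = 0.3 | r = 0.5 | r = 0.7 |
|---|---|---|---|
| Month-4 difference, any later course | 90% | 95% | 99% |
| Slope, sustained | 70% | 84% | 97% |
| Slope, half faded by month 12 | 18% | 23% | 35% |
| Slope, all faded, right direction | 0.9% | 0.7% | 0.5% |

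**The case against.** **The 12-month slope is an inference.** The screening sentence states no window and no time coding. A visit-wise arm-by-time contrast, or a change from baseline to month 4, would fit its words and remove the mismatch. Time coding is often left to an analysis plan. This stands in part: the article does not say that the screen spans 12 months. But it ties rate of change to all four visits for the primary outcome, sets it apart from the visit-wise comparisons, and names month 4 for the outcome while naming no visit for the mediator. A slope over all visits is the natural reading of a stated rule.

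**Early mediators are not lost as a class.** This stands. A sustained shift passes the slope screen in 70–97% of trials under the assumptions above. Only waning mediators are at risk. The evidence of waning concerns the effects of earlier interventions; the article gives no trajectory for any mediator.

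**Stronger readings that the article does not support:**
- *That the two conditions contradict the stated objective.* Study objectives speaks of mediators of the intervention effect and nowhere promises an unconditional test.
- *That requiring a significant total effect first is an error.* It is a recognised sequential strategy. It can miss indirect effects, but whether to drop it, or to add a multiplicity adjustment across mediators, is a matter of preference.
- *That screening on significance greatly inflates the reported indirect effects.* Selection inflates the statistic used to select, here the slope. At r = 0.5 the slope correlates only 0.09 with the baseline-adjusted month-4 difference (0.32 with the change score), so little of that inflation carries over to the month-4 path.
- *That unscreened mediators will be reported as not mediating.* The article says which mediators are analysed, not how the others are described.

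**Conclusion.** The point holds as a mismatch between the screening quantity and the mediated outcome. Read in the most natural way, the rule keeps most mediators whose early change lasts and drops most of those whose change fades: 18–35% pass if half the effect is gone by month 12, and under 1% in the right direction if all of it is, against 90–99% for a month-4 contrast. These powers rest on the assumed 0.4 SD shift, correlations of 0.3 to 0.7, compound symmetry and a linear time term. If the sponsor means a visit-wise or baseline-to-month-4 contrast, the loss disappears and only the wording needs repair. The primary efficacy conclusion is not touched.

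**What to change.** State that the intervention-to-mediator effect, and any screening on it, is the baseline-adjusted difference between arms in the mediator at month 4, the visit of the mediated outcome.

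Preferably also report the indirect effect with a confidence interval for all five named mediators (HIV knowledge, motivation, behavioural skills, collective self-esteem, and transgender adaptation and integration), whatever the screening result.

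The cost is a change of wording and a few extra models on data already being collected. No visit, measure or participant is added.
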